## 6.2 Qualitative

We will conduct semi-structured qualitative interviews (post-discharge interview guides) with each member of the RHH clinical care team and every patient and their caregiver 30 days after discharge. There is one post-discharge interview guide for clinicians and another post-discharge interview guide for patients and caregivers. The interviews will ask clinicians to reflect on their experience caring for home hospitalized patients, including their perceptions on quality and safety of care and comfort level. Clinicians will also be asked about their thoughts on home hospital technology and processes and their experience working with other clinical team members. The interviews with patients and caregivers will ask them to reflect on their experience being home hospitalized, their comfort level, and their perceptions on quality and safety of care provided. Patients and caregivers will also be asked to reflect on their experience with home hospital technology and their experience with the home hospital care team. All participants will be asked if they have any suggestions for improving rural home hospital.

The semi-structured interviews will be recorded, transcribed, and then analyzed using NVivo qualitative analysis software. We will audio record interviews using QuickTime on a Partners encrypted laptop and send them for transcription to a HIPAA-compliant transcription service (TranscribeMe).

Qualitative data will be analyzed using template analysis; two researchers will code the data independently. An initial codebook will be developed using deductive codes derived from the interview questions and the researchers' prior experience with rural home hospitals. Following initial coding, additional codes may be identified and added to the codebook. Inter-coder agreement will be assessed between the two coders and all inconsistencies will be noted, discussed, and resolved by consensus. Themes and recurrent patterns will be identified with any differences resolved by consensus. We will also use these data to improve home hospital operations.

## 7.0 RISKS AND DISCOMFORTS

### *Uncommon: Complications of surgical and non-surgical procedures*

Standard hospital procedures carry small risks and discomforts. For example, venipuncture can be painful and can lead to thrombophlebitis, but this is uncommon and readily rectifiable.

### *Uncommon: Device complications/malfunctions*

IV pumps, vital signs monitoring patches, and the other devices used during home hospital uncommonly have malfunctions.

### *Uncommon: Radiation risks*

Patients can receive radiography while admitted to home hospital, much the same as when they are admitted in the hospital. We do not anticipate that home hospital will in any way change the prevailing risk of radiation.

### *Common (but unchanged from usual care): Drug side effects and toxicities*

Drug side effects and toxicities do occur during inpatient medicine, despite following best practices and evidence based medicine. We do not anticipate that home hospital will in any way change the prevailing rate of drug side effects and toxicities compared to usual care. For example, acute kidney injury can occur in patients receiving antibiotics, even when correct dosing occurs. Home hospital is equipped to monitor and respond to the common drug side effects and toxicities much the same as the standard of care (monitoring, diagnostics, fluids, etc).

### *Common (but improved from usual care): Psychosocial risks*

Admission to the hospital can be a psychosocially difficult event, particularly for a senior. We believe home hospital will alleviate these typical risks.

## 8.0 POTENTIAL BENEFITS

### **Patients (home hospitalization group):**

- Remain in their home despite acute illness
  - Eat their own culturally concordant food
  - Sleep in familiar surroundings
  - Maximize time and interactions with their family and friends
- Improved health outcomes (we anticipate these from previous literature)
  - Reduced length of stay

- Reduced complications while admitted
  - Less delirium
  - Fewer falls
  - Fewer health care associated infections
  - Decreases reduction in functional status
- Improved patient experience
- Clinical improvements to the standard of care
  - Minimally invasive continuous vital signs, telemetry, and activity tracking;
  - On-demand 24/7 clinician virtual video visits;
  - Ambulatory/portable infusion pumps that can be worn on the hip;
- Improved transitions of care
  - Ability to coach patients on their post-discharge care plan in the appropriate environment, with caregivers available, and with adequate time for teaching given provider to patient ratio

#### **Caregivers:**

Possible benefits may include helping others in the future by participating in this study.

#### **Clinicians:**

Possible benefits may include helping others in the future by participating in this study

#### **Potential benefits to society**

- New evidence-based care paradigm for acute care hospitalization in rural US.
- Lower total medical expenditure. Allows for redirection of resources to areas in need.
- Might eventually lead to reduction in total hospitals in the US.
- Provide needed randomized controlled data on the rural home hospital intervention to inform payment methods moving forward.

## **9.0 MONITORING AND QUALITY ASSURANCE**

The BWH study team serves as this study's coordinating center. The study sites will be collecting the data and the BWH study team will be regularly monitoring data (not directly collecting data). There is a monitoring plan document attached to this study protocol which outlines in detail the monitoring steps that will be taken by the BWH study team and the study sites

#### *Safety monitoring*

If any of the following concerning safety events occur, a blinded monitoring committee will review the event to determine attribution to the intervention: fall with injury, medication error, DVT/PE, mortality during admission, transfer back to hospital (committee cannot be blinded for this endpoint).

If any of these events are felt to be due to the RHH intervention, they will be reported to the IRB with recommendations for appropriate actions to be taken. Decisions to modify the protocol or suspend the study will be made jointly by the study investigators, monitoring committee, and the IRB.

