### **2.2 Secondary Aims**

1. Demonstrate rural home hospital care improves days at home, physical activity, and readmission.

- For example: reduced length of stay, increased daily steps and hours of physical activity per day.

2. Synthesize lessons learned to prepare a dissemination guide for a future multi-site implementation.

- For example: clinical and administrative data including data collected from the process measures and qualitative interviews with patients and caregivers.
- Clinician process measures survey with rural home hospital clinicians
- Qualitative interviews with rural home hospital clinicians.

Please refer to our performance measures below for more details regarding the definitions and sources for each of these measures

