### 3.2 Exclusion

#### Patient exclusion criteria:

##### Patient exclusion clinical criteria:

- Acute delirium, as determined by the Confusion Assessment Method
- Cannot establish peripheral access by any means
- Secondary condition: active non-melanoma/prostate cancer, end-stage renal disease, acute myocardial infarction, acute cerebral vascular accident, acute hemorrhage (unless part of end of life pathway)
- Primary diagnosis requires multiple or routine administrations of intravenous narcotics for pain control
- Cannot independently ambulate to bedside commode, unless home-based aides are available
- As deemed by on-call MD, patient likely to require any of the following procedures that have not already occurred: computed tomography, magnetic resonance imaging, endoscopic procedure, blood transfusion, cardiac stress test, or surgery (unless these can be coordinated with appropriate facilities during the home hospitalization)
- For pneumonia:
  - Most recent CURB65 > 3: new confusion, BUN > 19mg/dL, respiratory rate ≥ 30/min, systolic blood pressure < 90mmHg, Age ≥ 65 (<14% 30-day mortality)
  - Most recent SMRTO > 2: systolic blood pressure < 90mmHg (2pts), multilobar CXR involvement (1pt), respiratory rate ≥ 30/min, heart rate ≥ 125, new confusion, oxygen saturation ≤ 90% (<10% chance of intensive respiratory or vasopressor support)
  - Absence of clear infiltrate on imaging
  - Cavitory lesion on imaging
  - Pulmonary effusion of unknown etiology
  - O2 saturation < 90% despite 5L O2
- For heart failure:
  - Has a left ventricular assist device

- GWTG-HF (>10% in-hospital mortality) or ADHERE (high risk or intermediate risk 1)\*
- Severe pulmonary hypertension
- For complicated urinary tract infection:
  - Absence of pyuria
  - Most recent qSOFA > 1 (SBP≤100 mmHg, RR≥22, GCS<15 [any AMS]) (if sepsis, >10% mortality)
- For other infection
  - Most recent qSOFA > 1 (SBP≤100 mmHg, RR≥22, GCS<15 [any AMS]) (if sepsis, >10% mortality)
- For COPD
  - BAP-65 score > 3 (BUN>25, altered mental status, HR>109, age>65) (<13% chance in-hospital mortality): exercise caution
- For asthma
  - Peak expiratory flow < 50% of normal: exercise caution
- For diabetes and its complications
  - Requires IV insulin
- For hypertensive urgency
  - Systolic blood pressure > 190 mmHg

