#### Safety

| Measure                                | Source                                                                                                                                                                          | Day(s) Obtained |
|----------------------------------------|---------------------------------------------------------------------------------------------------------------------------------------------------------------------------------|-----------------|
| Fall                                   | RA via MD/RN for home patients; MD EHR review for inpatients                                                                                                                    | Daily           |
| Delirium                               | RNs in home and inpatient settings calculate the CAM (standard of care in both). RA will obtain the home patient CAM via the home RN; RA will obtain the inpatient CAM via EHR. | Daily           |
| DVT/PE                                 | RA via MD/RN for home patients; MD EHR review for inpatients                                                                                                                    | Daily           |
| New pressure ulcer                     | As above.                                                                                                                                                                       | Daily           |
| Thrombophlebitis at peripheral IV site | As above.                                                                                                                                                                       | Daily           |
| Hospital Acquired Condition     |                                                                                                                                                                                 |                 |
| CAUTI                                  | As above.                                                                                                                                                                       | Daily           |
| Clostridium difficile                  | As above.                                                                                                                                                                       | Daily           |

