|                                        |                                                              |           |
|----------------------------------------|--------------------------------------------------------------|-----------|
| MRSA                                   | As above.                                                    | Daily     |
| New arrhythmia                         | As above.                                                    | Daily     |
| Hypokalemia                            | As above.                                                    | Daily     |
| Acute kidney injury                    | As above.                                                    | Daily     |
| Medication error                       | As above.                                                    | Daily     |
| Unanticipated mortality                | As above.                                                    | Daily     |
| Loss of consciousness                  | As above.                                                    | Daily     |
| Transfer back to hospital a | RA via MD/RN                                                 | Discharge |
| Unplanned mortality during admission   | RA via MD/RN for home patients; MD EHR review for inpatients | Discharge |
| Unplanned 30-day mortality             | RA via pt/caregiver call                                     | +30       |

a: intervention arm only

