Secondary outcomes require slightly larger samples sizes at 80% power (with Type 1 error of 1%, approximately the type 1 error when using the Benjamini-Hochberg method as noted above). For Cost, discharge to 30-days, using a gamma regression model similar to total costs, with 66 patients in each arm, we have 80% to see an expected 65% reduction in the mean for intervention to control (we assume the over-dispersion parameter for the gamma distribution variance is 2.8 as seen from our preliminary data). For number of hours per day laying down (equivalently, % of day Lying down), using a negative binomial regression model with a logistic link with treatment and site effects, with 66 patients in each arm, we have over 90% to see an expected 65% reduction in the number of hours lying down for intervention to control (we assume the over-dispersion parameter for the negative binomial distribution is 1.4 as seen from our preliminary data). For percent with 30-day readmission, using logistic regression model with treatment and site effects, with 66 patients in each arm, we have 80% to detect on odds ratio of 0.25 for intervention on control (assuming the percent 30 day readmission in controls is 23% as seen in preliminary data). For the number of days at home, using a log-normal distribution with treatment and site effects, with 66 patients in each arm, we have over 80% to see an expected 65% increase in the number days at home for control to intervention (from 29 days to 48, days assuming the over-dispersion parameter for the negative binomial distribution is 1.4).

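### The blinded attribution review covers only deaths during admission although 30-day mortality is a safety endpoint, and non-death safety events have no collection point after discharge

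*Protocol*

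**What the plan says.** Four parts of the protocol bear on this.

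- **Review list (9.0, Safety monitoring).** A blinded committee reviews certain events to "determine attribution to the intervention: fall with injury, medication error, DVT/PE, mortality during admission", and also transfer back to hospital, for which it cannot be blinded. Events judged due to the intervention are reported to the IRB. Death appears once on the list and is limited to the admission.
- **Safety endpoints (5.5.3, Safety table).** "Unplanned 30-day mortality" is obtained at +30. Only "Transfer back to hospital" is footnoted as intervention-arm only, so 30-day death applies to both arms. Its source is "RA via pt/caregiver call", with no EHR check named. Most other rows use "RA via MD/RN for home patients; MD EHR review for inpatients" and are obtained daily.
- **Expected stay and complications.** Section 2.2 gives as an aim "For example: reduced length of stay, increased daily steps and hours of physical activity per day". Section 8.0 also anticipates a shorter stay at home and fewer complications while admitted, naming delirium, falls and infections.
- **Other reporting (9.0, Adverse event reporting guidelines).** The DSMB receives unanticipated problems, including the events on the review list, and a six-monthly safety summary drawn from medical records. No time window is stated, and detailed procedures are left to a Monitoring Plan.

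**The concern.** Discharging a patient too early from the home is one plausible way for this model to fail, and its worst result is a death in the days after discharge. The protocol follows patients to 30 days and counts such deaths, yet its independent attribution step stops at discharge. That step is the one that leads to an IRB report and possible changes to the study.

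The second issue is the observation window for the other safety events. If these are counted only during the admission, the arm with shorter stays has less time in which to record an event. The complications that section 8.0 expects to fall would then appear to fall somewhat even at equal daily risk.

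**Working it through.** The protocol gives no figure to reproduce here. The check is a comparison of its tables, followed by one illustration.

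**1. Safety table by collection time (5.5.3).** There are 17 rows.

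| Rows | Daily | Discharge | +30 | Total |
|---|---|---|---|---|
| Non-death | 13 | 1 | 0 | 14 |
| Death | 1 | 1 | 1 | 3 |
| All | 14 | 2 | 1 | 17 |

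The only row that reaches past discharge is 30-day mortality.

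**2. Does daily mean during admission?** In the Health Care Utilization table of the same section, imaging, laboratory orders and note counts are marked as both daily and +30. Where collection continues after discharge, the protocol says so. A plain daily entry therefore reads as in-admission only.

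**3. Review list against endpoints.** The list in section 9.0 has five items. One is a death item, limited to admission; none is a 30-day item. Fall with injury, medication error and DVT/PE carry no time limit in the list, but their only collection in the Safety table ends at discharge. A pulmonary embolism a week later would surface only as a readmission or an ED visit.

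**4. Source for 30-day death.** It rests on a patient or caregiver call. Caregiver participation is optional (3.1), so a call that goes unanswered may be a missed contact or a death. For 30-day readmissions and ED visits, the utilization table already cross-checks the call against the EHR.

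**5. Effect of unequal windows (illustration; all inputs assumed).** Let p be a daily event risk that is the same in both arms and d the days of stay. The probability of at least one event is 1 − (1 − p)^d. Take p = 2%, with stays of 5 days in hospital and 4 at home:

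- hospital: 1 − 0.98^5 = 9.6%
- home: 1 − 0.98^4 = 7.8%
- ratio: 7.8 / 9.6 = 0.81

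This is an apparent 19% relative reduction with no difference in daily risk. For small p the ratio tends to the ratio of the stays, 4/5. If home stays were the longer ones (5 versus 4 days), the ratio would be 9.6 / 7.8 = 1.23, so the direction reverses.

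**The case against.** Several points on the other side are sound.

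- **Post-discharge outcomes are compared.** A reader might infer that deaths and harms after discharge go uncompared. The document does not support that. Thirty-day death is collected in both arms, unplanned 30-day readmission is a secondary endpoint with a planned logistic regression (5.5.2, 6.1), and ED visits and observation stays are collected at +30. The power section even sizes the readmission comparison, "assuming the percent 30 day readmission in controls is 23% as seen in preliminary data". Harm that leads to death, readmission or an ED visit is captured.
- **There is no general 30-day risk horizon.** The pneumonia limit carries the note "<14% 30-day mortality", which might suggest one. The heart failure and COPD scores in the same list (3.2) use in-hospital mortality. The mismatch rests on the 30-day mortality row itself, not on eligibility.
- **Other review routes may exist.** The DSMB rule includes the listed events but is not limited to them, so an unplanned death after discharge could qualify as an unanticipated problem. The Monitoring Plan may say more. It cannot be asserted that such deaths are never reviewed.
- **The window is partly a legitimate choice.** These are exploratory endpoints, and the denominator can be settled in the SAP. Catheter infection, IV-site thrombophlebitis and in-admission delirium are hazards of the admission. If a shorter stay produces fewer of them, that is partly a real effect. Daily clinician or EHR ascertainment is also more reliable than recall at 30 days.

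What remains is that the review list is closed, restricts death to the admission, and does not match the protocol's own 30-day death endpoint. Neither the DSMB rule nor the reference to the Monitoring Plan clearly resolves that. The two items on the list that can readily surface late, fall with injury and DVT/PE, also have no collection point after discharge.

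**Conclusion.** The point holds as a mismatch between the review list and the safety endpoints, and is worth correcting because the correction is cheap. Under the text of section 9.0, a death within 30 days of a home-hospital discharge does not trigger blinded attribution review, although it is a safety endpoint in both arms. Separately, 0 of 14 non-death safety rows extend past discharge, so those counts mix risk with length of stay.

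The size in deaths cannot be given. The protocol states no expected mortality and no split of deaths before and after discharge. A reader might apply the 14% figure to all patients, but it belongs to the pneumonia score alone and is an upper bound there. The 9.6% versus 7.8% comparison shows only how the window effect works. Its inputs are assumed and its direction depends on which arm stays longer.

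The conclusion assumes that a plain daily entry means during admission, as the utilization table suggests, and that the Monitoring Plan does not already extend the review.

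**What to change.** 1. **Review list (9.0, Safety monitoring).** Replace the in-admission death item with death from randomisation to 30 days after discharge. If the Monitoring Plan already provides this, bring the protocol text into line with it.
2. **Source for 30-day death (5.5.3, Safety table).** Add the EHR cross-check already used for the +30 utilization rows to the present call-only source.
3. **Fall with injury and DVT/PE.** Add a +30 entry, using the existing 30-day contact and EHR check. Report each event both during admission and to 30 days after discharge.
4. **Admission-specific hazards.** Keep catheter infection, IV-site thrombophlebitis and in-admission delirium on the admission window.

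The cost is protocol wording, a few items added to a contact that already takes place in both arms, and a few more committee reviews. Some of those reviews will concern expected deaths, because end-of-life patients are eligible (3.1). The 30-day counts will also be somewhat diluted by unrelated post-discharge events, which is why the in-admission count should be kept beside them. Moving every safety row to a 30-day comparison would be a larger trade-off and is not needed to close the gap.

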#### *Outcomes monitoring*

The RHH MD and RHH RN/paramedics will review quality and safety data daily as part of a rapid logistics improvement process.

Weekly, the RHH MD and RHH RN/paramedic will huddle to review quality and safety data as part of a rapid logistics improvement process.

